#### Secondary outcome measures

We will use standard telephone interviews with patients to collect secondary outcomes measures 1 week (T1) and 1 year (T2) after the initial recruitment consultation. These include: screening intention (1 item, assessed at T1), knowledge about the test instructions and the objectives of the screening test, (2 items, assessed at T1 and T2), patient activation (13 items- assessed at T1 and T2). We will use a validated short form patient activation measure, already available in French [43, 44]. We will assess HL using the Newest Vital Sign [45] (6 items) and the “single item literacy screener” [46] (1 item) (both assessed at T1). We will evaluate decisional conflict with SURE (4 items, assessed at T1) [47]. Finally, we will assess the proportion of patients who complete colonoscopy after a positive FIT test result within 1 year (collected by each regional coordination center in collaboration with the health insurance body). We will also collect socio-demographic information: age, gender, comorbidities, mother tongue, marital status, length of time living in France, educational attainment, income bracket, whether help was required to complete the questionnaire, any previous screening tests completed and the EPICES (Évaluation de la Précarité et des Inégalités de santé dans les Centres d’Examens de Santé), a validated measure of deprivation and social health in French, with 11 self-reported items (assessed at T1) [46].

Secondary outcomes for GPs will include a translated 12-item questionnaire assessing self-reported HL knowledge, skills, and behavior, collected prior to the intervention training and 1 year post training for GPs in both trial arms. We will also collect demographic information: age, gender, type of practice (GP practicing alone or in a medical center), year of medical training and participation in (and details of) a lump-sum participation package, ROSP (la rémunération sur objectifs de santé publique), an incentivized public health initiative. Tables 1 and 2 summarize the outcome measures and data collection timepoints.

**Table 2 Tab2:** Outcome measures and data collection timepoints for GPs

Outcome measures	Timepoints	
	Immediately before the health literacy training	1 year after the health literacy training
Health literacy knowledge, skills, and behavior (12 items)	**X**	**X**
Demographics (6 items)	**X**	
**Total number of self-report items per timepoint**	**18**	**12**

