### Participation and recruitment procedures for trial entry

Within the 4 regional areas, clinical research assistants (CRAs) will work in collaboration with recruited GPs. Participants will be approached in primary care medical centers or at individual GPs’ offices by their doctor, a resident (“interne”), or another member of the medical center. Clinical staff will confirm eligibility (see Fig. 3) and obtain verbal consent. Once participants are recruited, CRAs will re-confirm verbal consent over the telephone and check whether they are able to complete the questionnaires alone or if they need assistance.

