### Ethical approval, consent and recruitment strategies

The trial has received approval from the local research ethics committee, the Comité d’Ethique de la Recherche (CER) at the University of Toulouse III Paul Sabatier, France (ref 2021–349, dated 8th March 2021). Eligible participants will be asked to read a brief information sheet written in plain language or have a resident, mediator/patient navigator or other member of medical staff read the information out loud to them. This is particularly relevant since participants targeted by the trial are likely to have lower HL and lower textual literacy. According to the French health research classification, the ethics committee’s requirement for consent for this study requires participants’ verbal consent only or ‘non-opposition’ consent. Participants recruited by an intervention GP will be given a pictorial brochure about CRC screening and asked to watch a 3-min video on a tablet before exiting the primary care center/GP’s office. Participants recruited by a GP in the control arm will discuss the trial and CRC screening in their usual way.

One week after (T1), the CRA will call participants and offer to conduct a standardized telephone interview where the questions will be read out loud to them. Whenever possible, T1 data collection will be carried out in a single phone call. If the participant does not answer the first telephone call, the CRA will make three further attempts to contact them and leave up to three voice messages. CRAs will verify telephone contact details with the recruiting GP practices. Given participants are likely to have lower HL, this is the best strategy to maximize retention and minimize participant burden and missing data.

One year after (T2), CRAs will call participants for the follow-up assessment and offer to conduct a further standardized telephone interview. As with T1, attempts to verify contact details and to call the participant several times will be made.

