### Outcome measures

#### Primary outcome measure

The primary outcome measure is CRC screening uptake assessed 1 year after the initial recruitment consultation (T2) by self-report questionnaire (see Table 1). Each CRCDC, in collaboration with the health insurance body (CPAM) in each region, will also provide data on CRC screening uptake at 6 months (for feedback to GPs in the intervention arm) and 1-year post enrollment.

**Table 1 Tab1:** Outcome measures and data collection timepoints for patients

Outcome measures	Timepoints	
	(T1) One week after the primary care consultation where CRC screening is discussed	(T2) 1 year after the CRC screening consultation
Number of eligible patients identified and successfully enrolled	**X**	
Number of patients enrolled who receive the patient-facing intervention	**X**	
Discontinuation rate		**X**
CRC screening uptake (primary outcome) with self-report item		**X**
Screening intention (1 items)	**X**	
Knowledge of CRC screening (2 items)	**X**	**X**
Patient activation (13 items)	**X**	**X**
Health literacy (7 items)	**X**	
EPICES (11 items)	**X**	
SURE (4 items)	**X**	
Was the questionnaire completed alone? (1 item)	**X**	**X**
Demographics (9 items)	**X**	
**Total number of self-report items per timepoint**	**48**	**17**

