### Statistical analysis

Initial examination of data will include descriptive statistics, frequency distributions, and histograms to identify outliers and missing data. The baseline data in each arm will be compared to ensure randomization was conducted successfully. We will use the Stata 16 software (Stata corp, US) to perform all analyses.

All participants will be asked to indicate at T1 if they have received the intervention to enable an intention-to-treat (ITT) and as-treated analysis. We will adopt a regression framework for all analyses as it allows seamless transition between basic analyses involving a single predictor and more complex analyses involving additional predictors (mediation variables, control covariates, time-trends, interaction terms or effect modifiers).

Further, the regression framework allows clustering of observations due to repeated measurements on patients across time, nesting of health professionals within sites, and patients within health professionals, to be accurately accounted for using mixed-effect regression models [53] or generalized estimating equations [54, 55].

### Analyses corresponding to aim 1

We will first perform separate analyses for each data collection period (T1 and T2) using linear and logistic regression models as appropriate for continuous (knowledge, patient activation, HL), and binary (screening intention, screening uptake, colonoscopy completed) outcomes respectively. The results will provide potentially valuable insights into how rapidly the intervention affects outcomes. Outcomes measured twice may also be analyzed using a longitudinal model. A secondary analysis that adds predictors for the number of patients seen by the healthcare professional in the intervention arms will examine whether there are physician learning effects. To gain insight into whether the intervention will be more effective according to the patient’s HL level and socioeconomic position, we will test the first order interaction between HL level/socioeconomic position and the intervention indicator variables. EPICES scores will also be used.

### Analyses corresponding to aim 2

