### Missing data

Most data collection will be via standardized telephone interview (at T1 and T2), which provides opportunities for preventing and monitoring missing data. We will investigate whether multiple imputation is required to cope with any missing baseline, interim, and outcome data.

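### All patient-reported baseline variables are taken only at the T1 call, one week after exposure, so consented patients who miss T1 have almost no individual covariates for the baseline comparison, the moderator analyses or imputation

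*Protocol article*

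**What the plan says.** **Order of events.** Practice staff confirm eligibility and take verbal consent (Participation and recruitment procedures for trial entry). In the intervention arm the patient material follows at the same visit: "Participants recruited by an intervention GP will be given a pictorial brochure about CRC screening and asked to watch a 3-min video on a tablet". Telephone contact comes later: "Once participants are recruited, CRAs will re-confirm verbal consent over the telephone". The T1 interview is at one week, with a first call and three further attempts (Ethical approval, consent and recruitment strategies).

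**What is collected when.** Under Secondary outcome measures: "We will also collect socio-demographic information: age, gender, comorbidities, mother tongue, marital status, length of time living in France, educational attainment, income bracket", followed by the help-needed item, previous screening tests and EPICES. Table 1 has two columns, T1 and T2, and the first is labelled "T1) One week after the primary care consultation where CRC screening is discussed". Demographics, EPICES and health literacy are ticked in that column only. Hypothesis 1.2 treats T1 as the baseline for health literacy.

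**How the data are used.** Statistical analysis: "The baseline data in each arm will be compared to ensure randomization was conducted successfully". The same section plans interactions of the intervention with health literacy and socioeconomic position. Heterogeneity of treatment effect adds education, age and gender. Missing data: "We will investigate whether multiple imputation is required to cope with any missing baseline, interim, and outcome data".

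**Counting.** Table 1 ticks "Number of eligible patients identified and successfully enrolled" at T1 and "Discontinuation rate" at T2. It gives no denominator for the latter. Changes to intervention allocation has the research assistants record refusals and discontinuations, with reasons, at every stage.

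**The concern.** A baseline measured after exposure, and only in those who answer the telephone, is not a baseline for everyone who entered the trial. Loss between the visit and T1 happens after randomization and after contact with a trained or untrained GP. It can therefore differ by arm and by past screening behavior, and past screening is itself one of the T1 items.

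Three uses of the data are exposed:

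- **Patient-level baseline comparison.** An imbalance among T1 responders could come from chance, from differential recruitment by unblinded GPs or from differential T1 response. The planned data cannot separate these.
- **Moderator and subgroup analyses.** Health literacy, EPICES, education, age and gender are all T1-only, so these analyses are confined to T1 responders or to imputed values.
- **Imputation.** For patients without T1, no scheduled patient-level baseline predictor exists, and previous screening is the most important absentee.

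Age, gender and education cannot be altered by a brochure, so for them the problem is who is missing, not what is measured.

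**Working it through.** **1. Does Table 1 really put everything at T1?** Its own totals confirm it.
- T1: 1 (intention) + 2 (knowledge) + 13 (activation) + 7 (health literacy) + 11 (EPICES) + 4 (SURE) + 1 (completed alone) + 9 (demographics) = 48, as stated.
- T2: 1 (uptake) + 2 + 13 + 1 = 17, as stated.
- The nine demographic items match the text: age, gender, comorbidities, mother tongue, marital status, time in France, education, income, previous screening. The help-needed item and EPICES have their own rows. Age, gender and previous screening are thus T1 interview items.

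**2. What is known about a consented patient with no T1?** Arm, GP or office, region, and that the eligibility criteria were met (so age 50 to 74). In addition, the screening centers, with the health insurer, supply uptake at 6 months and 1 year after enrollment (Primary outcome measure). That is an outcome, not a covariate.

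**3. How many patients could this be?** Planned attrition is 25% (Sample size and power calculation): 0.25 × 1024 = 256. The split before and after T1 is not stated.

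| Share of attrition before T1 (assumed) | Patients without T1 data |
|---|---|
| 0 | 0 |
| one third | 85 |
| one half | 128 |
| two thirds | 171 |
| all | 256 |

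**4. Illustration of bias with no true effect.** None of these inputs is in the documents. Assume 40% previously screened with 55% uptake, and 60% never screened with 14% uptake. True uptake in both arms is 0.4 × 0.55 + 0.6 × 0.14 = 0.304. Loss before T1 is 5% of the previously screened in both arms. Among the never screened it is 10% in the intervention arm and 20% in control. Only T1 responders are analyzed, and external uptake is ignored.
- Intervention: (0.4 × 0.95 × 0.55 + 0.6 × 0.90 × 0.14) / (0.38 + 0.54) = 0.2846 / 0.92 = 30.9%.
- Control: (0.4 × 0.95 × 0.55 + 0.6 × 0.80 × 0.14) / (0.38 + 0.48) = 0.2762 / 0.86 = 32.1%.
- Spurious gap: 1.2 points.
- With 30% loss of never-screened controls: (0.209 + 0.42 × 0.14) / 0.80 = 33.5%. The gap is 2.5 points.

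With equal arms, overall loss is (8% + 14%) / 2 = 11%, about 113 of 1024, in the first case. In the second it is (8% + 20%) / 2 = 14%, about 143. Both lie within the one-third to two-thirds range of step 3. As set up, the gap runs against the intervention; exchanging the loss rates between arms reverses it. Weighting the strata back to 40/60 restores 30.4% in both arms, but only because the example lets loss depend on nothing except arm and previous screening.

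**The case against.** The strongest reply is that the consequences are limited, and much of it stands.

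- **Uptake is not lost.** A reader might infer that patients missing T1 cannot be analyzed or usefully imputed. The documents do not support that. Uptake from the screening centers and the insurer does not depend on T1, and can serve as an outcome source or an imputation auxiliary alongside GP and region. Nor is the T2 call restricted to T1 responders. What remains is that the stated primary measure is self-report, the Missing data section gives the external data no role, and those data do not replace covariates or moderators.
- **Discontinuation.** A reader might infer from the T1 and T2 ticks that losses before T1 fall outside the discontinuation rate. That is not stated. The T2 tick may be only a reporting time, patients are described as recruited before the telephone call, and discontinuation is recorded at every stage. The flow diagram is not visible in the text available. The most that can be said is that no denominator is given.
- **Randomization check.** A reader might infer that the whole check rests on responders after exposure. It does not. GPs or offices are the randomized units, and Table 2 takes GP data before training. The weakness is confined to the patient-level comparison.
- **Enrollment form.** A condensed article may omit what the practice writes down at consent. That is fair, but the article does assign age, gender and previous screening to the T1 interview.
- **Size.** The illustration's inputs are invented, and it counts every T1 non-responder as lacking the outcome. That is correct, and it is offered only for scale.

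**Conclusion.** The point holds in a limited form. The schedule places every patient-reported baseline variable one week after exposure and makes it conditional on a completed call. Consented patients who miss that call have no individual covariates beyond arm, GP, region and eligibility range. The patient-level baseline comparison, the moderator and subgroup analyses and the imputation of covariates are weakened accordingly. The uptake analysis is much less affected, provided the external uptake data are used.

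The number of patients concerned depends on how the planned 25% attrition divides around T1, which the documents do not say. The size of any bias cannot be derived from them either. Under the assumptions shown it is about 1 to 2.5 points, small beside the 15-point target difference, and its direction depends on which arm loses more. This is a reason to improve a stated schedule at low cost, not a threat to the trial as a whole.

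**What to change.** 1. Obtain age, sex and previous screening for every patient who consents at the practice. The screening centers' files are preferable if they hold these items, because that avoids entry by practices that know their allocation. Otherwise record them on the enrollment form before the brochure and video are given.
2. Use these variables in the patient-level baseline table for all consented patients. Use them, together with the external uptake data, in the imputation model.
3. In Table 1, take all patients consenting at the practice as the denominator for discontinuation, and report losses before T1 and before T2 by arm.

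**Cost.** A few data fields per patient in a data extract or on the enrollment form, and an edit to Table 1. The reported discontinuation rate may look less favorable. If the enrollment form is used, practice staff spend a little time per patient, and because practices are unblinded, ascertainment of screening history could differ by arm. Health literacy and EPICES would still be missing for patients who never complete T1, but could be imputed from better predictors than GP and region alone.

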### GP recruitment

To recruit GPs, we will first use a purposive sampling approach to include a balance of male and female GPs, practicing alone and in medical centers, in each region. GP work addresses will be coded against the EDI to establish if their practice covers a geographically disadvantaged area (EDI 4 or 5). GPs will be approached by email or telephone and given information about the trial. If this approach fails, we will transition to a convenience sampling approach, using contacts in our research network. Confirmation of participation will be by email and further contact details obtained. GPs will be randomly allocated to the control or intervention arm prior to the intervention training process, 2 months before patient recruitment begins. If a participating GP leaves their practice or decides to leave the trial, we will recruit another GP and assign him or her to the same arm.

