### Intervention

We will translate and adapt (using a translation procedure adapted from TRAPD) an intervention previously developed and evaluated in a randomized controlled trial conducted in the US to address HL and improve CRC screening [33]. This intervention combined a 2-h HL and CRC screening training targeting GPs and a patient level intervention consisting of a short brochure and video. To maximize generalizability and implementation, we will develop a 2 h e-learning HL training in French and a one-hour booster session similar to the previous trial’s intervention [33]. The first hour will be an online course that will primarily include didactic teaching using videos. The second hour will consist of a c-MOOC (Connectivist – Massive Online Learning Course), an online classroom model, where all participating GPs in the intervention group can interact with each other and with a trained facilitator from our team, experienced in HL training ([name]). This interactive session will build on the content provided in the initial didactic session. The c-MOOC is based on a learner-driven dialogue where participation, discussions and reflection on the content presented are the intended focus. It will also include small group discussions and role-playing sessions focused on empowering GPs to discuss CRC screening effectively with their patients. A 1-h c-MOOC booster training session will be held 6 months later. During this session, GPs will receive data on their screening uptake rates over the previous 6 months, a reminder of practical strategies to communicate with patients with lower HL skills in busy, high-volume primary care practices. They will also have the opportunity to engage in small group discussions. Each GP in the intervention arm will receive 150 euros for completing the first 2-h learning training (1 h didactic learning + 1 h c-MOOC) and 75 euros for completing the booster session (1 h c-MOOC).

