### Randomization

#### Sequence generation, type of randomization and allocation concealment

We will use an R script written by the trial statistician to perform the GP randomization. The random allocation sequence will be concealed until interventions are assigned. We will use block randomization to ensure a balanced allocation of each cluster (GP or GP office) in each region to the intervention and control arms. Participants recruited by GPs will therefore be a priori allocated to either the control or intervention arm by virtue of the GP that has recruited them. GPs will not be required to assess HL or deprivation levels (as these are not a inclusion or exclusion criteria) as the GP practice itself has already been identified as being located in a disadvantaged area.

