### Blinding

Due to the nature of intervention delivery, it will not be possible to blind GPs to their allocation to either the control or intervention arm. At the individual level, patients invited to participate in the trial will likely be unaware that they are in the intervention or control arm. Furthermore, the CRAs collecting participants’ primary outcome data, assessing outcomes and conducting the analyses will not know to which group participants were allocated. The data analyst will also be blinded to arm allocation.

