### Health economic assessment

A cost-effectiveness analysis will be conducted to assess the medico-economic impact of implementing the intervention among patients with lower HL in disadvantaged areas of the four targeted regions. The purpose of this analysis is to compare the costs related to the effectiveness of the intervention with health professionals (the 2-h HL training) and users (brochure and video) versus usual care (control arm). First, we will calculate the cost per additional CRC screening performed by dividing the difference between the costs of implementing the intervention and the cost of the usual care group, relative to the observed increase in testing in the intervention group. Second, we will calculate the cost per new cancer diagnosed in patients with a positive screening test. The time horizon of the analysis will be the duration of the study (1 year).

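### The GP self-rated baseline is taken after allocation, and both GP time points are tied to a training that control GPs are not described as receiving

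*Protocol article*

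**What the plan says.** The Secondary outcome measures section has the 12-item GP questionnaire "collected prior to the intervention training and 1 year post training for GPs in both trial arms". Table 2 is more specific: the first completion, with six demographic items, is "Immediately before the health literacy training", and the second is "1 year after the health literacy training". Hypothesis 2 judges improvement in these self-ratings against that first measurement.

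On allocation, the GP recruitment section states that "GPs will be randomly allocated to the control or intervention arm prior to the intervention training process, 2 months before patient recruitment begins". The Randomization section adds: "The random allocation sequence will be concealed until interventions are assigned". The Blinding section accepts that "it will not be possible to blind GPs to their allocation to either the control or intervention arm".

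The training is described for the intervention arm only. The Intervention section states that "Each GP in the intervention arm will receive 150 euros for completing the first 2-h learning training", with a further 75 euros for the booster session. The control condition is usual care (Abstract; Health economic assessment), and no delayed training for control GPs is described. A GP who leaves is replaced by another in the same arm (GP recruitment).

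**The concern.** A baseline serves as a reference only if allocation cannot have influenced it. Here the measure is a subjective self-rating, and the stated order puts it after allocation. A GP about to start a paid course may rate current skills lower than otherwise, or may already have prepared and rate them higher. A control GP who knows that no course is coming has neither reason. Any such shift enters the comparison with baseline and cannot be told apart from an effect of training. Willingness to return the questionnaire could also differ by arm once the arm is known, although nothing in the article shows that it would.

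The second part concerns timing. Both time points are defined relative to the training, yet they are applied to both arms. As written, neither has a reference date of its own for control GPs, so the two arms could be measured at different calendar times or over different intervals.

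At stake is the GP questionnaire, the one GP outcome that the article names for Aim 2.

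**Working it through.** **Order of events.** No design figure is in dispute, so the first check sets the passages side by side.

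1. Allocation comes before the training process and 2 months before patient recruitment (GP recruitment).
2. Concealment ends when interventions are assigned (Randomization).
3. GPs are not blinded (Blinding).
4. The first questionnaire comes directly before the training (Table 2).
5. The training is given, and paid for, in the intervention arm (Intervention).
6. The second questionnaire comes 1 year after the training (Table 2).

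Steps 1 and 4 put the baseline after allocation unless allocation and training are practically simultaneous. Steps 2, 3 and 5 make it very probable that GPs know their arm by then: an intervention GP on the point of starting a course that only that arm receives will in practice know it. This last step is an inference. For replacement GPs the arm is fixed before they join, so their baseline cannot precede allocation under any timing.

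**Size of the possible bias.** The inputs are:

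- GPs per arm: n = 16, from the planned minimum of 32 GPs (Sample size and power calculation), assuming equal arms.
- Allocation-driven shift in one arm's baseline: s = 0.3 SD. This is an assumption, with a range of 0.2 to 0.5.
- Correlation between baseline and follow-up: r = 0.5. This is an assumption, with a range of 0.3 to 0.7.

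Bias is given below in absolute size; its sign is opposite to that of s when the shift is in the intervention arm.

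Change-score contrast between arms:

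- Bias = s = 0.30 SD.
- Standard error = sqrt(2(1 − r)) × sqrt(2/n) = sqrt(2 × 0.5) × sqrt(2/16) = 1 × 0.354 = 0.354 SD.
- Ratio = 0.30 / 0.354 = 0.85 standard errors.

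Baseline-adjusted contrast between arms:

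- Bias = r × s = 0.5 × 0.3 = 0.15 SD.
- Standard error = sqrt(1 − r²) × sqrt(2/n) = sqrt(0.75) × 0.354 = 0.306 SD.
- Ratio = 0.15 / 0.306 = 0.49 standard errors.

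Over the assumed ranges, the change-score bias runs from 0.2 to 0.5 SD. The adjusted bias runs from 0.3 × 0.2 = 0.06 SD to 0.7 × 0.5 = 0.35 SD.

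For scale, the difference detectable with 80% power at two-sided 0.05 is (1.96 + 0.84) × sqrt(2/16) = 0.99 SD, by the normal approximation, for a score with unit SD.

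**The case against.** The strongest reply is that the article never says when GPs learn their arm. The sentence on the questionnaire, and Hypothesis 2, require only that it come before the training, which would allow completion before disclosure or even before randomization. Only the column heading in Table 2 says otherwise. This stands to the extent that knowledge of the arm is inferred and must be worded so. It does not remove the point, because the table gives the more exact timing and that timing is hard to fit with a measurement before allocation.

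On the time points, the interactive session is shared by the intervention GPs, so its calendar date could be applied to control GPs. That is possible, but the article does not say so, and the training as written is not an event in the control arm.

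On size, a reader might infer that the estimate is off by nearly one standard error. That holds only for an unadjusted change score under assumed inputs. The article does not commit to a change score, and its regression framework allows covariates. Adjustment brings the figure to about half a standard error, and a comparison of 1-year scores alone would carry no bias from the baseline. A 0.3 SD shift is also well below the 0.99 SD detectable difference.

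A reader might also infer that the effect of training would be overstated. The documents do not support a direction, since rating oneself lower before a course and preparing for it push opposite ways.

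Finally, the 1-year self-rating is itself unblinded, and response bias there enters every analysis. That is correct, and moving the baseline does not touch it.

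**Conclusion.** The point holds with limits. Followed as written, Table 2 gives a baseline taken after allocation and very probably with knowledge of the arm, and it defines both time points by an event that control GPs are not described as having. The order of allocation and measurement rests on the text; knowledge of the arm is a close inference from it.

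The possible bias is moderate: 0.30 SD (0.85 standard errors) for a change score or 0.15 SD (0.49 standard errors) with baseline adjustment, given an assumed 0.3 SD shift, r = 0.5 and 16 GPs per arm. Whether a shift would occur, and in which direction, cannot be known from the article.

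A reader might carry the concern over to the trial's main result. That is not supported: the primary outcome is patient screening uptake, and neither it, its sample size nor any patient outcome uses the GP questionnaire. The consequence is confined to the secondary GP comparison under Aim 2. The change is still worth making before GPs are allocated, because no later analysis can recover a pre-disclosure baseline that was not collected.

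**What to change.** Have each GP complete the 12 items and the demographic items when confirming participation, which the article already plans by email, and disclose the arm only afterwards. For a replacement GP, collect the questionnaire before that GP is told which arm he or she will join. Time the 1-year follow-up in both arms from one common date, such as allocation, and reword both column headings in Table 2 and the matching sentence under Secondary outcome measures.

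The cost is small: the same questionnaire is sent earlier, no sample-size figure changes, and the interval from baseline to follow-up becomes slightly longer. Disclosure to replacement GPs needs a short written step. The change removes one source of bias only, so the report should still describe the 1-year GP result as an unblinded self-rating.
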